## Abstract

**Background:**

Exercise therapy in patients with hip and/or knee osteoarthritis is effective in reducing pain, increasing physical activity and physical functioning, but costly and a burden for the health care budget. A web-based intervention is cheap in comparison to face-to-face exercise therapy and has the advantage of supporting in home exercises because of the 24/7 accessibility. However, the lack of face-to-face contact with a professional is a disadvantage of web-based interventions and is probably one of the reasons for low adherence rates. In order to combine the best of two worlds, we have developed the intervention e-Exercise. In this blended intervention face-to-face contacts with a physical therapist are partially replaced by a web-based exercise intervention. The aim of this study is to investigate the short- (3 months) and long-term (12 months) (cost)-effectiveness of e-Exercise compared to usual care physical therapy. Our hypothesis is that e-Exercise is more effective and cost-effective in increasing physical functioning and physical activity compared to usual care.

**Methods/Design:**

This paper presents the protocol of a prospective, single-blinded, multicenter cluster randomized controlled trial. In total, 200 patients with OA of the hip and/or knee will be randomly allocated into either e-Exercise or usual care (physical therapy). E-Exercise is a 12-week intervention, consisting of maximum five face-to-face physical therapy contacts supplemented with a web-based program. The web-based program contains assignments to gradually increase patients’ physical activity, strength and stability exercises and information about OA related topics. Primary outcomes are physical activity and physical functioning. Secondary outcomes are health related quality of life, self-perceived effect, pain, tiredness and self-efficacy. All measurements will be performed at baseline, 3 and 12 months after inclusion. Retrospective cost questionnaires will be sent at 3, 6, 9 and 12 months and used for the cost-effectiveness and cost-utility analysis.

**Discussion:**

This study is the first randomized controlled trial in the (cost)-effectiveness of a blended exercise intervention for patients with osteoarthritis of the hip and/or knee. The findings will help to improve the treatment of patients with osteoarthritis.

**Trial registration:**

NTR4224.

## Background

Osteoarthritis (OA) is worldwide one of the leading causes of pain and disability. Most common affected sites are the hip and knee joints [1]. In the United States, prevalence of knee OA for patients of 45 years or older is 17 percent and prevalence of hip OA 10 percent [2]. In the Netherlands, it is estimated that 312.000 persons suffer from knee OA (19.1/1000) and 238.000 from hip OA (14.5/1000) [3]. Presumably, these prevalence rates are underestimated since these data are solely based on general practice patients’ registrations [3]. OA is an age-related disease and besides pain and disability characterized by morning stiffness, reduced range of motion, instability of the joint and loss of health related quality of life [4, 5]. These symptoms induce that people with hip and/or knee OA are physically less active than the general population [6, 7]. In the long term, physical inactivity may lead to functional decline and psychological problems [8, 9].

Exercise therapy is the widely recommended non-pharmacological intervention in patients with hip and/or knee OA [10–13]. Therapeutic exercise, most of the time provided by a physical therapist, can consist of strengthening exercises, functional task-oriented exercises and/or aerobic training [10]. Many studies have shown the effectiveness of exercise therapy on patients’ physical functioning in daily life, for example stair climbing, rising from a chair or getting in or out a car [14, 15]. Besides, exercise therapy is effective in reducing patients’ levels of pain and increasing their physical activity [14, 15]. Unfortunately, the face-to-face contacts with a physical therapist are costly and a burden for the health care budget. To illustrate, Dutch healthcare costs related to OA were about 1,112 million euro in 2011 [16]. Likewise, the prevalence of hip and knee OA is expected to increase with 52% in 2040, due to the aging population and an increasing number of obese people [3]. In order to regulate OA costs there is a need for more (cost)-effective strategies to manage hip and/or knee OA.

The internet has created new possibilities to combine face-to-face care with online care, called blended healthcare [17]. The partial substitution of a web-based intervention for exercise therapy sessions is hypothesized to result in a (cost)-effective intervention in many ways. In the first place, a blended intervention will result in lower costs since the average number of physical therapy sessions for patients with OA will decrease. A second advantage of a blended intervention is the 24/7 online support for exercises at home. Support in exercises at home is important since adherence to self-directed exercise is a common problem in exercise therapy [18, 19]. Research highlighted the importance of adherence to exercises at home, since this positively influences treatment effects on pain and physical functioning [19]. Third, a well-designed web-based intervention in which patients’ can report their experiences with home exercises provides physical therapists information about patients’ individual needs for guidance.

Up till now, previous research in web-based interventions has focused on interventions without human support. Unfortunately, the effects of these interventions are small, especially in the long-term [20–24]. These modest effects can partly be explained by the absence of personal guidance [17]. To illustrate, in the study by Bossen et al. [23], patients cited that the lack of face-to-face contact in a self-guided web-based intervention was an important reason to discontinue. Hence, the combination of a web-based intervention with face-to-face contact has been recommended by several researchers [20, 25, 26]. To date, there are no studies investigating the (cost)-effectiveness of a blended intervention in the physical therapy setting. Therefore, we have developed e-Exercise and have planned to evaluate and implement this blended intervention. The intervention will be based on the Dutch “KNGF guideline OA hip-knee” for physical therapists [10]. The web-based part will be an adapted version of the previously developed and evaluated online PA program Join2Move [24], a web-based intervention for OA patients without support of a physical therapist. The aim of this study is to determine the (cost)-effectiveness of e-Exercise compared to usual care (physical therapy). Our first hypothesis is that e-Exercise will be more effective in terms of increasing PA and improving physical functioning in patients with hip and/or knee OA as compared to usual care. The second hypothesis is that e-Exercise will be cost-effective in comparison to usual care by physical therapists. The research question of this RCT study is: What is the short- (3 months) and long-term (12 months) (cost)-effectiveness of e-Exercise in patients with hip and/or knee OA on PA and physical functioning in comparison to usual care?

## Methods/Design

### Study design

A prospective, single-blinded, multicenter cluster randomized controlled trial (RCT) will be conducted. The study has been approved by the Medical Ethical Committee of the St. Elisabeth hospital Tilburg, the Netherlands (Dutch Trial Register NTR4224). The e-Exercise intervention will be compared with usual care (i.e. physical therapy). A flow diagram of the study protocol is shown in Figure 1.

**Figure 1 Fig1:**
[figure not shown]
**RCT study procedures.**

### Participants

#### Physical therapists

A stratified random sample of 800 physical therapy practices in three provinces of the Netherlands (e.g. Noord-Holland, Utrecht and Gelderland) will be invited by letter to participate in the study. Contact information of physical therapy practices will be obtained from the national database for physical therapists of the Netherlands Institute for Health Services Research (NIVEL). Additionally, a recruitment advertisement will be placed in the online newsletter of The Royal Dutch Society for Physical Therapy (KNGF). Each participating physical therapy practice will be asked to enroll one or two physical therapists. The researchers will recruit 100 physical therapists. Inclusion criteria for physical therapists will concern: (i) practicing in primary care, (ii) treating at least six patients with OA of the hip and/or knee each year. Physical therapists practicing in another physical therapy practice participating in the study will be excluded.

#### Patients

In order to include 200 participants, each physical therapist is requested to recruit about two patients. Since the study of Veenhof et al. [27] showed that recruitment of OA patients in the physical therapy practice is difficult and research has shown that different recruitment strategies do not affect treatment outcomes [28], this study uses various recruitment strategies. First, patients with hip and/or knee OA who visit a physical therapy practice will be invited to participate in the study. Second, recruitment advertisements will be placed in local newspapers. Third, information letters and flyers will be sent to general practitioners. Responders to these articles and flyers will be allocated to the nearest participating physical therapist. Eligibility criteria of patients interested in the study concern: (i) age 40–80 years, (ii) OA of the hip and/or knee according to the clinical criteria of the American College of Rheumatology (ACR) [29]. Exclusion criteria will include: (i) being on a waiting list for a hip or knee replacement surgery, (ii) being contra-indicated for PA without supervision, (iii) being sufficiently physically active according to the physical therapist, (iv) participation in a physical therapy and/or PA program in the last six months, (v) no access to internet, (vi) inability to understand the Dutch language. The diagnostic ACR clinical criteria for knee OA are: knee pain and at least three of the following six criteria: age > 50 years, morning stiffness <30 minutes, crepitation, bony tenderness, bony enlargement and no palpable warmth. Diagnostic ACR clinical criteria for hip OA are: hip pain and hip internal rotation < 15 degree and hip flexion ≤ 115 degree; or hip internal rotation ≥ 15 degree and pain on hip internal rotation and morning stiffness of the hip ≤ 60 minutes and age > 50 years [29]. Contra-indications for PA will be determined using the adapted Physical Activity Readiness Questionnaire (PAR-Q) [30]. This questionnaire is used to identify patients for whom PA is inappropriate.

### Study procedure

Physical therapists willing to participate in the study will be screened on in- and exclusion criteria by a researcher (CK). Cluster randomization will be performed at the level of the participating physical therapy practices that will randomly be assigned to the intervention (e-Exercise) or the control group (usual care) by means of a computer-generated random sequence table. Physical therapists will receive a half day training about e-Exercise and the study procedure (intervention group) or about practicing according to the “KNGF guideline OA hip-knee” [10] and the study procedure (control group). Physical therapists will inform eligible patients about the study and screen them on in- and exclusion criteria. All suitable patients will be stimulated to contact the research team by telephone, e-mail or reply card. After an informative phone call with one of the researchers (CK or DB), interested patients will receive a letter about the trial and a request to complete an informed consent form. Patients recruited by the additional recruitment strategies (i.e. advertisements in newspapers and flyers from the general practitioner) will be informed by the researchers before they visit their physical therapist. Physical therapists in both groups will be asked to record the content of their treatment on a registration form. During the study period, both patient groups will continue their medication and usual care managed by other caregivers.

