### Blinding

In this single-blind study , the physical therapists are not blinded since they will treat patients according to the randomization. The researchers will be blinded to group allocation until completion of the statistical analyses. Participants will be assigned to a unique digital trial code to ensure that treatment outcome measurement and statistical analysis will be performed blind to treatment allocation. Patient information will be stored in a separate database.

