**Table 1 Tab1:** **Description e-Exercise intervention**

Intake	Physical therapist	Anamnesis and physical examination
		Assessment in- and exclusion criteria
		Providing information about osteoarthritis, e-Exercise and study
		Scheduling a follow-up appointment for week 1
	Patient	Reading patient information letter
		Signing an informed consent
		Completing baseline measurement
Start e-Exercise		
Week 1	Physical therapist	Providing information about osteoarthritis and e-Exercise
		Providing information about the 3-day baseline self-test
		Instruction of the 4 stability/mobility exercises
	Physical therapist & Patient	Registration on website to participate in e-Exercise
		Online selection of central activity and 4 stability/mobility exercises
		Providing information about the 3-day baseline self-test
		Scheduling a follow-up appointment for week 2
	Patient	Signing online treatment agreement
		Performance of a 3-day baseline test
		Performance of 4 stability/mobility exercises
Week 2	Physical therapist	Providing information about physical activity and pain
	Physical therapist & Patient	Evaluation results from the 3-day self-test
		Determining short-term goal
		Discussing the gradual increase of the selected activity
		Evaluation stability/mobility exercises
		Scheduling a follow-up appointment for week 6
	Patient	Performance of online module 1, each module consists of:
		- Gradually increase selected activity
		- Video home exercises
		- Video/text self-management themes
Week 3-5	Patient	Online modules 2-4
Week 6	Physical therapist & Patient	Evaluation online modules 1-4
		Discussing the upcoming steps and weeks
		Evaluation stability/mobility exercises
		If necessary, scheduling an additional treatment between week 7-11
		Scheduling a follow-up appointment for week 12
	Patient	Online module 5
Week 7-11	Patient	Online modules 6-10
Week 12	Physical therapist	Discussing long-term goals
		Support to maintain a physically active lifestyle
	Patient	Online module 11

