Although the study is well-considered, we take into account potential operational issues. First challenge is the recruitment of sufficient numbers of physical therapists. Since e-Exercise is characterized by fewer physical therapy sessions, physical therapists will receive less reimbursement from health insurances compared to usual care. To deal with this challenge, accreditation points for participating physical therapists will be supplied in order to make study participation more attractive. Another incentive is that physical therapists keep their access to the website after the study is finished. The second challenge is the non-usage of the web-based part of e-Exercise. Previous studies have indicated that participants in online interventions are less motivated and feel less pressure to continue compared to traditional face-to-face interventions [59]. However, in order to stimulate website usage, we will incorporate email reminders into the program. But most importantly, since this study concerns a blended intervention, which is a combination of face-to-face contact with e-health, e-Exercise is expected to maximize adherence compared to self-guided internet interventions [17, 23].

There are several strengths in the design of this study. First, we elaborate on the study results of Joint2Move [24]. This intervention showed to be an effective web-based intervention for patients with OA of the hip and/or knee and will be the fundament for e-Exercise. Second, the primary outcome measurements PA and physical functioning will be measured subjectively (questionnaires) and objectively by means of accelerometers and the timed “Up & Go test”. Third, the 12-month follow-up will result in data about long-term effectiveness. The last strength is that e-Exercise will be evaluated in daily physical therapy practice, the setting in which the intervention will be implemented after the presented trial. Therefore, user experiences can be used in order to improve e-Exercise and to facilitate implementation.

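### Therapists who know their arm screen patients, one exclusion rests on their opinion of activity level, and in the e-Exercise arm baseline is listed after the programme is described

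*Protocol article*

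**What the plan says.** **Allocation.** Protocol article, Study procedure: "Cluster randomization will be performed at the level of the participating physical therapy practices". Therapists then attend a half-day training whose content depends on the arm. The Blinding section confirms that "the physical therapists are not blinded since they will treat patients according to the randomization".

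**Identification of patients.** The Study procedure section continues: "Physical therapists will inform eligible patients about the study and screen them on in- and exclusion criteria". Suitable patients then contact the research team, have a phone call with a researcher, and receive a letter and consent form. Under Patients, "each physical therapist is requested to recruit about two patients". Most criteria there are factual or use a named instrument (age range, ACR criteria, PAR-Q, waiting list, recent programme, internet access, language). One is not: "being sufficiently physically active according to the physical therapist".

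**Second route.** Advert and flyer responders are informed by the researchers before seeing a therapist, and are assigned to the nearest participating one.

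**Intake.** Table 1, which describes the e-Exercise arm only, lists among the therapist's intake tasks "Providing information about osteoarthritis, e-Exercise and study". The patient's tasks are then the letter, consent and, last, the baseline measurement. No equivalent table is given for usual care.

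**Analysis.** The Effectiveness section adjusts for baseline values and for confounders, with age, OA location and gender as examples.

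**The concern.** Randomising practices makes the practices comparable. It does not protect the comparability of patients chosen afterwards by someone who knows the arm. Two things could go wrong.

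1. **Differential recruitment.** A therapist who knows whether the patient will get a largely home-based programme or conventional sessions may invite, or exclude as active enough, different kinds of patient. The activity exclusion is the clearest opening: it has no threshold or instrument, and physical activity is a primary outcome.
2. **Arm-influenced baseline.** HOOS/KOOS and SQUASH are self-reports. If they are completed after the patient has heard which treatment is coming, expectation can colour the answers. Those answers are then used as covariates.

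At stake is whether a difference between arms, in outcomes or in costs, can be attributed to e-Exercise rather than to who entered each arm.

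**Working it through.** No figure in the plan is at issue, so the check is mainly of sequence.

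**Step 1: order of events on the practice route.** Study procedure gives randomisation of practices, training by arm, therapist information and screening, contact with the research team, researcher call, then letter and consent. This is narrative order, not dated steps. It agrees with the arm-specific training, with the Blinding section, and with the Timeline, where practices are recruited from May 2014 and the trial starts in September 2014. No step identifies patients before randomisation, and no one unaware of the arm screens them. The researcher call comes after the therapist has decided whom to approach.

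**Step 2: order on the advert and flyer route.** Researchers inform first, which is a real safeguard. The patient then goes to a therapist whose practice already has an arm. The article does not say whether the activity judgement is made before or after that visit.

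**Step 3: when the patient learns the arm.** In the e-Exercise arm, Table 1 puts the description of e-Exercise among the intake tasks and lists baseline last. In the control arm the order is not stated.

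**Step 4: what adjustment can do.** Write the adjusted difference as D = (Y1 − Y0) − β(B1 − B0), where Y and B are the arm means of outcome and baseline and β is the baseline slope.
- If recruitment differs only in true baseline level, the second term removes most of the resulting difference.
- If it differs in a factor that B and the other covariates do not capture, such as motivation, that part stays in Y1 − Y0.
- If knowledge of the arm shifts reported baseline in one arm by δ, D moves by βδ in absolute size. Adjustment then carries the error into the estimate.

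**Step 5: sensitivity of the trial to a residual shift (illustration only).** Inputs from Sample size: 200 patients, 20% loss, two-sided 0.05. Assuming equal arms, n = 200 × 0.8 / 2 = 80 per arm. The shift b, in SD units of the outcome, is an assumption; there is no true effect, and clustering is ignored. The noncentrality is λ = b / √(2/80) = b / 0.158, and P(reject) = 1 − Φ(1.96 − λ) + Φ(−1.96 − λ).

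| Assumed b | λ | P(reject) |
|---|---|---|
| 0 | 0 | 0.050 |
| 0.1 | 0.63 | 0.097 |
| 0.2 | 1.26 | 0.244 |
| 0.3 | 1.90 | 0.475 |

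A shift of 0.2 equals the lower end of the target effect range (0.2 to 0.4). The table shows what a shift of a given size would do. It is not evidence that such a shift will occur.

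**The case against.** The case for the plan has substance. Only one criterion is worded as opinion. The internet exclusion applies in both arms, which limits differences in computer access. Advert and flyer patients hear from researchers first. Consent follows a researcher call and letter. The model adjusts for baseline values, the adjustment most relevant to selection on activity level, and its confounder list is open-ended. All of this stands and narrows the concern.

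The caseload does not prove room to choose either. Therapists must treat at least six such patients a year and are asked for about two. If enrolment runs about four months (September to December 2014), the minimum caseload yields 6 × 4/12 = 2. Choice exists only above that minimum.

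Three stronger readings are tempting but not supported:

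- **That baseline follows disclosure of the arm throughout the trial.** Table 1 covers e-Exercise only and groups tasks by actor, so it is not a strict chronology. The study flow diagram is not shown.
- **That the plan admits a motive for selective enrolment.** The Discussion says "physical therapists will receive less reimbursement from health insurances compared to usual care", but as an obstacle to recruiting therapists, with accreditation points as the response. A link to choosing patients is an inference, and its direction is unknown.
- **That every endpoint is biased by some fixed fraction of an SD.** The document gives no basis for a size. An imbalance in a prognostic factor reaches an outcome only as far as the two are related, which would differ across TUG, SQUASH, accelerometry, HOOS/KOOS and costs.

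Finally, a log of patients approached and the wording of the letter may well be in the full protocol. Their absence from an article is not a fault.

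**Conclusion.** The point holds in a limited form. The article states that unblinded therapists, trained by arm, inform and screen patients, and that one exclusion is their own opinion in a primary outcome domain. For e-Exercise patients it also lists baseline as the last patient step of an intake at which the therapist describes the programme. The stated safeguards reduce the risk but cannot correct who was approached on the practice route, factors no covariate captures, or a baseline already affected by knowledge of the arm.

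Neither the size nor the direction of any bias can be estimated from the document. The conclusion rests on reading the Study procedure section as chronological, which the other sections support. It is worth acting on because the remedy is cheap and changes steps the plan already contains.

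**What to change.** 1. **Order of intake, both arms.** Complete consent, baseline questionnaires and accelerometry before the therapist tells the patient which treatment the practice gives. Use the same information letter in both arms, covering both treatments. Amend Table 1 accordingly and state the control-arm order.
2. **Activity exclusion.** Replace the opinion-based wording with a fixed, pre-stated self-report rule applied identically in both arms, with the threshold set by the investigators. The researcher can check it at the existing phone call. Therapists keep the ACR examination, which cannot be done by phone.
3. **Count.** Keep a per-practice tally of eligible and approached patients and report it by arm. The call comes too late to change who was approached, so the tally is what would make selective invitation visible.

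The cost is a slightly longer intake and a short form; the call already takes place. These changes reduce the risk without removing it: therapists still know their arm when they approach patients, and the baseline timed Up & Go is still measured by the unblinded therapist.
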